## Secondary outcomes

### ***Unimanual capacity***

i. Jebsen Taylor Test of Hand Function (JTTHF)

The JTTHF measures unilateral speed and dexterity on timed tasks [81]. The test measures speed and accuracy of performance on various complexities of grasp and release. The original test was designed and validated in adults and typically developing children and has been modified to exclude the writing task and reduced the maximum allowable time of each of the remaining six tasks to two minutes when utilised in children with congenital hemiplegia [25,75,82,83]. The JTTHF has been shown to be responsive to change due to an intervention [74]. There are concerns regarding the stability of test-retest performance in the unimpaired limb [74,75,82,83]. The test retest reliability and concurrent validity of the JTTHF with the Box and Blocks Test in children with congenital hemiplegia will be determined as part of the COMBiT study.

ii. Box and Blocks Test (BBT)

The BBT is a measure of gross manual dexterity [84]. It was initially developed specifically for use in adults with cerebral palsy the test comprises of a wooden box (53.7 cm × 25.4 cm) which is divided by a 15.2 cm high partition to form two equal compartments. 150 coloured wooden blocks all 2.5 cm in size are placed in one compartment. The participant is required to transfer as many blacks from one compartment to the other in 60 seconds. The score is the number of wooden blocks transferred in one minute [84,85]. Concurrent validity of the BBT is supported by a good correlation with the Minnesota Rate of Manipulation Test (r=0.91) and the General Aptitude Test Battery, Part 10 (r=.86). Inter rater reliability of the BBT was r = 1.00 and r = 0.999 for the right and left hands respectively. The reported test-retest reliability of the BBT (at six months) is ρ = 0.976 and 0.937 for right and left hands respectively [84]. Norms for 6–19 year olds are available [84].

## Bimanual performance

(i) Children’s Hand-Use Experience Questionnaire (CHEQ)

The CHEQ is a Rasch analysed questionnaire for children and youth (6 to 18 years) that examines their experience of using their impaired hand during bimanual activities [86]. Participants are required to answer twenty nine questions related to bimanual activities and identify their level of independence and whether one or two hands are used to complete the task. Three scales of perceived efficacy of grasp, time taken to complete the activity and degree of feeling of being bothered doing the activity are also rated for each of the bimanual activities. Summary scores for the questions can be generated, but for participants in a research trial, raw data will be transformed into logit scores by the test developers [86]. The CHEQ has not yet been used in clinical trials, and its sensitivity to change will be examined as part of the COMBiT study.

### ***Participation outcomes***

(i) Assessment of Life Habits (LIFE-H for children version 1.0)

The LIFE-H® [87] is designed for children aged 5 to 13 years and measures life habits in home, school and neighbourhood environments [87]. It is a questionnaire completed by the parent/caregiver about the child. The long form consists of 197 items divided into 12 categories and includes regular activities (eating meals, communication, and mobility) and social roles. A weighted score ranging from 0 to 10 is generated for each category and overall total. Construct validity was established during test development [87] and criterion validity with strong correlations between the LIFE-H and PEDI and Functional Independence Measure for Children (WeeFIM) are reported [88]. Adequate to excellent internal consistency (Cronbach’s α = 0.73 – 0.90 for categories, 0.97 for daily activities and 0.90 for social roles), intra-rater (ICC = 0.83 – 0.95 for daily activities), inter-rater (ICC = 0.8 – 0.91 for daily activities and 0.63 – 0.9 for social roles) and test-retest reliability (ICC = 0.73 for total score) have been established [89]. Four categories, reflecting the particular areas of difficulty in hand use and independence in daily life typically experienced by children with hemiplegia, will be evaluated in this study including nutrition (eg. mealtime activities), personal care (eg. dressing), education and recreation.

### ***Quality of life outcomes***

(i) The Cerebral Palsy Quality of Life questionnaire for children (CPQOL-child)

The CPQOL will be used to investigate quality of life from the perspectives of parents (CPQOL Primary Caregiver Questionnaire) and from the children themselves (children and youth of nine years or older- the CPQOL Child Report Questionnaire) [90]. The CPQOL-Child is a condition specific measure across seven broad domains of quality of life: social wellbeing and acceptance, functioning, participation and physical health, emotional wellbeing, access to services, pain and impact of disability and family health. Psychometric properties of the CPQOL are excellent with Cronbach’s α ranges from 0.74-0.92 (parent proxy report) and 0.80-0.90 (child self report) [91]. Adequate test re-test reliability (ICC = 0.76-0.89) is reported with moderate correlations with the CHQ, KIDSCREEN, and GMFCS. The CPQOL-teen version for youth 14–18 years has adequate correlations with a generic QOL instrument for both parent report (r = 0.40-0.46) and teen self report (r = 0.58-0.68) [92,93].

## Individualised occupational performance goals

(i) Canadian Occupational Performance Measure (COPM):

The COPM is a standardised individualised, client centred measure that evaluates client’s self-perception of occupational performance over time [94]. Participants identify areas of difficulty in everyday occupational performance across the domains of self-care, leisure and productivity and rate their performance and satisfaction for each problem on a scale from one to 10 [94]. An average score for performance and satisfaction is calculated. There is good evidence of construct, content and criterion validity [95-97]. The retest reliability of the performance and satisfaction scores on the COPM is high (ICC = 0.76-0.89) [98,99]. The COPM has demonstrated responsiveness to change in paediatric clinical trials [100,101] with a 2 point change on COPM performance reported as being clinically significant [94]. In the present study, the COPM will form the basis of goal setting for therapy. The COPM will be administered by one of the study occupational therapists. Children aged 8 years and older will be encouraged to identify three to five goals and rate their perceived level of performance and satisfaction on the 10-point scale in collaboration with their primary caregivers. For younger children or those with intellectual impairment, parent/caregivers will complete the COPM with input from their child.

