### Randomisation

Following baseline assessments, children will be randomised within matched pairs to receive either COMBiT or standard care. To maximise homogeneity of the sample and minimise group differences at baseline, matching in pairs will be completed according to age (12 month bands), gender, and Manual Ability Classification System (MACS) level [30]. Treatment allocation will be recorded on a piece of folded paper inside a concealed opaque envelope. Using a sequence of computer-generated random numbers the number “1” or “2” will be allocated to each member of the pair. As each pair is randomised, they will be allocated the next consecutive envelope, which will be opened by non-study personnel who will read and record the treatment allocation. Study personnel will be informed of group allocation.

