### Study procedure

Children will attend either the Royal Children’s Hospital or The University of Queensland in Brisbane for baseline and follow up assessments. Children randomised to COMBiT will participate in a two week day camp during school holidays commencing within one month of baseline assessments. Participants randomised to standard care will be allocated a local therapist and individual therapy sessions will commence within one month of baseline assessments. The experimental design and outcome measures are depicted in Figure 1.

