COMBiT will be conducted over two weeks of the school holidays in a “day camp model”. Participants will attend a community facility “Flipside Circus” for six hours a day, five days a week from 9am to 3pm. In total, 45 hours of the day camp program will directly target upper limb training, and 10 hours will provide indirect use of the UL in more general gross motor upper limb activities. For both mCIMT and BIM training, the content will include intensive activity based practice, circus activities as well as self-care and recreational activities. The group will be led and supervised closely by five to seven therapy staff to achieve a ratio of one trainer to two children. Five core occupational therapists and one physiotherapist will plan and lead all intervention groups. Daily grading of activities and modification of tasks for the participants in each group will be performed by the core therapists. Tasks and activities will focus on reducing upper limb activity limitations identified at baseline assessment and target three occupational performance goals identified by the parents and/or child. Planning activities for each group will require task analysis, and develop guidelines for grading to challenge children with varying capabilities. Specific details of the content of the COMBiT weekly program contents are presented in Additional file 1: Table S1. Prior to commencement of the daily program, staff will be briefed and given specific tasks with written instructions outlining how each activity will be performed for the specific children they are supervising. Professional circus trainers will lead the two hour circus workshops. The core therapy team will meet with the circus trainers to design these programs and at the end of each session to discuss and modify the program as required and provide guidance to grading of tasks for participants. A debriefing session for the entire COMBiT group with staff members and separately for the staff and volunteers will be conducted at the conclusion of each day. The core therapy team will also meet daily to review individual participants’ goals and continually grade their program. A daily record of attendance will be kept and anecdotal information from the day will also be recorded.

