## Blinding

Functional MRI data will be qualitatively analysed by neurologists masked to group allocation. Paediatric neurologists with fMRI training will independently rate scan quality (0–5), region of activation, change over time and patterns of reorganisation. Data for AHA and MUUL will be rated from videos masked to order and group allocation.

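### No masked assessment is provided for JTTHF, BBT or COPM, although study personnel are told the allocation; the primary AHA and MUUL comparison is not affected

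*Protocol article*

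**What the plan says.** All references are to the protocol article.

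- **Blinding.** Two items are masked. For imaging: "Functional MRI data will be qualitatively analysed by neurologists masked to group allocation". For the primary outcomes: "Data for AHA and MUUL will be rated from videos masked to order and group allocation". The Primary outcomes section repeats the masking for AHA and MUUL. No other measure is named.
- **Randomisation.** After non-study personnel open the envelope and record the result, "Study personnel will be informed of group allocation". No exception is stated for outcome assessors.
- **Individualised occupational performance goals.** "The COPM will be administered by one of the study occupational therapists". The same section says: "In the present study, the COPM will form the basis of goal setting for therapy". The scores come from the family: "Children aged 8 years and older will be encouraged to identify three to five goals and rate their perceived level of performance and satisfaction", with caregivers completing the measure for younger children.
- **Secondary outcomes, Unimanual capacity.** JTTHF is a timed test and BBT a one-minute count. Neither description names an assessor, masking or scoring from video.
- **Who treats.** For the day camp: "Five core occupational therapists and one physiotherapist will plan and lead all intervention groups". For the comparator: "Participants randomised to standard care will be allocated a local therapist".

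**The concern.** The article treats assessor knowledge as a risk for AHA and MUUL, whose raters are masked to both group and order, but gives the other hands-on or interview-based measures no comparable protection. JTTHF and BBT can be influenced by how the child is encouraged, when timing starts and stops, and what counts as a completed transfer. The COPM is a rating given in an interview about the very goals that therapy worked on. If the person collecting these data at follow-up knows the allocation, a difference between arms on these measures cannot be cleanly separated from assessor influence.

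The staffing could also make the exposure unequal. Camp groups are led by the core therapists, whereas standard care is delivered locally. A camp family could therefore be interviewed by someone who worked on its goals, and the same is less likely for a standard care family.

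At stake is the interpretation of two secondary unimanual measures and the individualised goal measure. The Background includes individualised outcomes in the open question that motivates the trial.

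**Working it through.** **1. Sections side by side**

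| Measure | How it is scored | Masking stated | Assessor stated |
|---|---|---|---|
| AHA | from video | yes, group and order | two certified raters |
| MUUL | from video | yes, group and order | experienced occupational therapist |
| fMRI, qualitative | from scans | yes, group | neurologists |
| JTTHF | timed | none | none |
| BBT | count in 60 seconds | none | none |
| COPM | self or caregiver rating, by interview | none | a study occupational therapist |

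**2. Who knows the allocation.** The Randomisation sentence cannot cover literally everyone, because the AHA and MUUL raters are masked elsewhere. Those raters and the neurologists are the only exceptions the article creates. A study occupational therapist administering the COPM falls within study personnel and outside the exceptions.

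**3. When it can matter.** Randomisation follows the baseline assessments, so baseline scores cannot be affected. The exposure is confined to follow-up. The Abstract gives 13 and 26 weeks, but the schedule for each measure is in Figure 1, which is not shown. The visits at which COPM, JTTHF and BBT are repeated therefore cannot be confirmed.

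**4. What it does not touch.** Statistical analyses bases the primary comparison on AHA and MUUL. The named secondary analyses are LIFE-H and CP-QOL domains.

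**5. Scale, as an illustration only.** The article gives no figure for assessor bias, so there is none to reproduce. Inputs are 25 per group and alpha 0.05 (Sample size), with a two-sided test assumed. Let b be an assumed systematic shift between arms, in SD units, when there is no true effect. Using a normal approximation and ignoring the matching:

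- standardised shift d = b / √(2/25) = b / 0.2828
- false-positive rate = 1 − Φ(1.96 − d) + Φ(−1.96 − d)

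| b (assumed) | d | false-positive rate |
|---|---|---|
| 0 | 0 | 5.0% |
| 0.1 | 0.354 | 6.4% |
| 0.2 | 0.707 | 10.9% |
| 0.3 | 1.061 | 18.6% |
| 0.5 | 1.768 | 42.4% |

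The rate is the same whichever arm the shift favours. The table shows sensitivity to an assumption and does not estimate what will happen in this trial.

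**The case against.** The strongest reply is that a condensed article need not say who administers each secondary test, and that the staffing inferences go beyond the text. Much of this stands:

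- No assessor is named for JTTHF or BBT. A reader might infer that they are left to staff who know the allocation. The text supports only that no masked assessment is provided.
- The sentence on COPM administration sits among the goal-setting sentences and may describe baseline work. Who collects the follow-up ratings is not stated.
- The article never equates the study occupational therapists with the core camp therapists. A reader might infer that camp staff re-interview their own families and that the bias must favour COMBiT. The text does not exclude the first, but it does not state it, and the direction does not follow.
- A reader might take JTTHF and BBT as corroboration for the primary hypothesis. No section says so.
- Families know which treatment they had. A masked interviewer would leave the COPM raters themselves unmasked.
- The 2-point COPM figure is a clinically significant change reported for performance. It is not a between-arm margin, so it cannot be used to size an interviewer effect.

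The point is still more than silence in a short article. There is a dedicated masking section with a specific list, a positive statement that study personnel know the allocation, and a positive statement of who administers the COPM. Together these describe an arrangement, and it leaves the three measures unprotected.

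**Conclusion.** The concern holds in limited form. As the article stands, JTTHF, BBT and COPM have no masked assessment, and nothing keeps staff who know the allocation, possibly including camp therapists, from assessing them at follow-up. The conclusion rests on reading the Blinding list as complete and on taking the Randomisation sentence to include staff who are not expressly masked.

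It is confined to two secondary measures and the individualised goal measure. The primary AHA and MUUL comparison is not affected. Neither the size nor the direction of any bias can be derived from the article, so a claim that these outcomes will favour COMBiT is not supported. The weakness is worth correcting because the correction is cheap, but it does not threaten the trial's main conclusion.

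**What to change.** 1. **Randomisation:** state that only personnel delivering treatment are told the allocation.
2. **Secondary outcomes (Unimanual capacity) and Blinding:** state that JTTHF and BBT are filmed at the same visit as the MUUL, which is already videotaped, and are timed and counted from video by the existing raters, masked to group and order.
3. **Individualised occupational performance goals:** state that follow-up COPM ratings are collected, where existing staffing allows, by someone not involved in that child's treatment, and that families are asked not to disclose allocation.
4. **Interpretation:** describe the COPM as an unmasked self-report outcome.

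The cost is some extra video-scoring time, with no added visits. Step 3 may be hard to meet in full. Recruitment blocks of 24 to 26 children, half allocated to each arm, give 12 to 13 children per camp, which fits a single group of 10 to 15, and the core therapists lead every group. If they are also the study occupational therapists, no uninvolved one may be available. Video scoring does not remove the effect of encouragement in the room, and some families will still disclose their allocation.

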## Environmental measures

(i) Study questionnaire

A study questionnaire has been developed to capture demographic information that has been shown in the literature to influence a child’s outcomes. Information will be collected on child’s age and gender, socio-economic status, family structure and supports, family income and current involvement in rehabilitation programs.

(ii) The Parenting Scale

The Parenting Scale [102] is a 30-item questionnaire measuring three dysfunctional parenting styles: laxness (permissive, inconsistent discipline); over-reactivity (harsh, emotional, authoritarian discipline and irritability); and verbosity (lengthy verbal responses) [103]. All 30 items are scored on a seven point scale, with low scores indicating good parenting practices and high scores indicating dysfunctional parenting. The Parenting Scale will be completed by the primary caregiver during baseline assessments and an overall measure of laxness, over reactivity and verbosity will be calculated. The total scaled score (the sum of all items divided by 30) will be used as the primary measure of parenting style in analyses. The Parenting Scale has demonstrated adequate internal consistency (α’s for subscales ranging from 0.78 to 0.85), good test-retest reliability (r = 0.84 for the total score), an ability to discriminate parents of clinic versus non-clinic children, and correlations with observed parenting style and child behaviour [102-104].

## Motivation

(i) The Dimensions of Mastery Questionnaire (DMQ)

The DMQ provides a primary caregiver’s and child’s self-perceptions of mastery motivation [105]. It consists of 45 items across seven subscales and two aspects of mastery motivation. Instrumental mastery focuses on persistence with tasks and includes the subscales of object-oriented persistence, gross motor persistence, social persistence with adults and social persistence with peers. Expressive mastery comprises subscales of negative reactions to failure and mastery pleasure. The final subscale, competence, is considered a separate construct which measures the child’s ability to master tasks relative to peers [105]. The DMQ takes approximately 15 minutes to complete and will be administered with both children and their primary caregivers according to standard administration procedures. This involves rating each of the 45 items on a five point scale ranging from 1=not at all typical to 5=very typical. Three is considered to be average for a typically developing child of the same age. Higher scores are considered to represent higher levels of motivation [105]. To assist with understanding in the younger age group (5 to 7 years) children may be prompted with ‘smiley faces’ representative of the scores 1=not at all typical through to 5=very typical. Seven individual subscale scores are calculated by summation of items in the subscale and dividing by the number of items to obtain an average score between 1 and 5. A total persistence score between 1 and 5 can be calculated from the average of the four instrumental subscales. A total mastery motivation score between 1 and 5 can also be calculated based on the average of the four instrumental subscales and the mastery pleasure subscale. The DMQ total motivation score (average of the four instrumental subscales and mastery pleasure) will be used as the primary measure of motivation as the DMQ total motivation score is representative of the child’s overall motivational predisposition including both instrumental and expressive mastery motivation. Individual DMQ subscale scores will be examined in secondary analyses. Test construction and clinical utility of the DMQ is satisfactory. The DMQ has high item internal consistency with Cronbach’s α‘s greater than 0.74 [105]. Test retest reliability for parents of preschool aged children is reported as high with ICC’s between 0.74 and 0.82 on instrumental subscales. Total score ICC’s are 0.76 with a standard error of measurement (SEM) of 7.31 [106]. Construct validity is strong with clear factorial evidence for scales on principal component analysis [106]. The psychometric properties and clinical utility of this measure have recently been evaluated as part of a systematic review of measures of motivation in school aged children with a physical disability or motor delay [107]. The test retest reliability of DMQ parent proxy report in school aged children will be investigated as part of this study.

(ii) The Pediatric Volitional Questionnaire (PVQ)

The PVQ is an observational assessment whereby the child’s volition is scored according to motivation and mastery behaviours observed during different activities [108]. This requires therapy sessions to be videotaped so that the child’s motivation and mastery behaviours when faced with therapy tasks of varying challenge can be observed. The PVQ has a four point scoring system where 1=passive through to 4=spontaneous. A mean level of volition ranging between 1 and 4 is calculated by summing all scores and dividing by the number of items (i.e. 14). The methodological quality of psychometric studies for the PVQ is poor based on very small samples sizes. Within these studies, the PVQ demonstrated adequate evidence for construct and criterion validity with Rasch analysis identifying good item spread (-0.96 to 1.34 logits) and no misfitting items [109]. Mean difficulty of items (0.00±0.66) and mean ability of participants (0.68±0.99) was well spread [109]. Reliability of the PVQ was weak with evidence of poor inter rater reliability (rater separation 4.11) [109]. For this project, the PVQ will be rated by the same rater. The psychometric properties and clinical utility of the PVQ measure will be evaluated as part of this study.

